## Objectives

The primary objective of the PAM-CNO trial is to investigate the efficacy of intravenous pamidronate in reducing pain in adult CNO patients. Secondary objectives are to evaluate the effect of pamidronate on (1) a variety of patient-reported outcome measures (PROMs), (2) biochemical and immunological indices relevant to CNO, and (3) radiological parameters of disease activity and severity. Additional objectives are to evaluate baseline predictors of treatment response, to elucidate mechanisms by which pamidronate may reduce pain in CNO, and cost-effectiveness.

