### Eligibility criteria

Patients ≥18 yr of age with an established diagnosis of CNO are the population base of this study. In the absence of validated classification criteria for CNO, the primary diagnostic criterion is sterile bone inflammation at one or more skeletal sites in the anterior chest wall, with or without involvement of other skeletal sites. This is identified based on clinical features (inflammatory bone pain and possibly signs of inflammation on physical exam), biochemical markers (mild to moderate increase in inflammation markers, though often these are within normal range), and imaging findings (bone marrow edema, sclerosis, hyperostosis, erosions, ligament ossification, ankylosis of joints, and increased isotope uptake on nuclear imaging). If a bone biopsy is performed, histopathology compatible with sterile bone inflammation includes nonspecific inflammation and increased bone turnover. Sterile bone inflammation, and herewith diagnosis of CNO, is confirmed through a multidisciplinary, integrated assessment. Of note, this definition of sterile bone inflammation/CNO means that patients can have varying skeletal distribution patterns and may or may not have additional (extra)skeletal features such as arthritis, enthesitis, sacroiliitis, palmoplantar pustulosis, psoriasis, or severe acne.

Further inclusion criteria are as follows:

Score for maximal pain (concerning bone pain at lesion sites over the past week) ≥6/10 as measured by Brief Pain Inventory (BPI).^30^Insufficient response to at least one NSAID/COXIB at maximum approved and tolerated dosage, intolerance or contraindication to these agents, or indication for direct second-line treatment due to active vertebral lesions.A washout period of prior bisphosphonates (6 mo since last administration).

Exclusion criteria are as follows:

<18 yr of age.Active pregnancy wish, active pregnancy, or nursing.Generalized pain without pain at the site of CNO lesions.Bisphosphonate allergy.Estimated glomerular filtration rate < 30 ml/min.Uncontrolled endocrine comorbidities, active cancer (treatment), or other severe comorbidity preventing the attendance of study visits.Severe language barrier preventing the completion of questionnaires.Mental disability.

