### Outcomes and statistical analyses

The primary outcome of this trial is score of maximal pain on BPI (numerical rating scale 0-10) measured at the end of the 6-mo randomized phase. We will compare the difference between groups by generalized linear mixed model (GLMM) with analysis of covariance (ANCOVA) to account for baseline scores. The primary analysis will be intention-to-treat (see Table 1 and Figure 2). Secondary outcomes include a range of patient-reported,^32^^-^^40^ biochemical, and radiological outcomes, as well as their intercorrelation, baseline factors associated with treatment response,^41^^,^^42^ and cost-effectiveness^43^ (see Table 1 for measurement instruments, statistical analyses, and timepoints). Sensitivity analyses include a per-protocol and an as-treated analysis of the primary outcome. Missing data on the outcomes not evaluated by GLMM are imputed and handled through maximum likelihood techniques. No interim analyses are conducted.

**Table 1 TB1:** Primary and secondary outcomes of the PAM-CNO trial.

	**Outcome**	**Instrument**	**Timepoint of collection**	**Statistical analysis**	**Timepoint of analysis**
**Primary**	Score for maximal pain at CNO lesion sites	BPI	0, 3, 6, 9 and 12 mo	GLMM with ANCOVA	6 mo
**Secondary**	Score for minimal, average, and activity-related pain at CNO lesion sites	BPI	0, 3, 6, 9 and 12 mo	GLMM with ANCOVA	6 and 12 mo
**PROMs**	Shoulder function	SFA			
		SRQ			
	General health	SF-36			
	Quality of Life	EQ-5D			
	Work activity	Work Activity Score			
	Physical activity	IPAQ			
	Fatigue	MVI-20			
	Patient global	PGIC			
	Burden of a relative	Carer-QoL			
	Pain diary	NRS 0-10 for pain	2 d per wk, for entire 1-yr trial span	GLMM	6 and 12 mo
	Achievement of mild pain, as defined by ≤4/10 for maximal pain on BPI	BPI	0, 3, 6, 9, and 12 mo	Chi-square between groups, reported as odds ratio with 95% confidence interval	3, 6, and 12 mo
	Achievement of ≥50% reduction in maximal pain on BPI	BPI	0, 3, 6, 9, and 12 mo		
	% of patients with reduction in standard dose of NSAIDs/COXIBs	-	3, 6, and 12 mo		
**Biochemical**	ESR, CRP	Standard laboratory evaluation	0, 3, 6, 9, and 12 mo	GLMM with ANCOVA	6 and 12 mo
	Pro- and anti-inflammatory cytokines	ELISA			
	Bone markers	ELISA			
	mRNA expression	MLPA	0, 6, and 12 mo		
	T-lymphocyte counts	FACS			

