**Radiological**	Progression or regression of either sclerosis, hyperostosis, erosions, ankylosis, or soft tissue calcification	[^18^F]NaF-PET/CT	0, 6, and 12 mo	Chi-square between groups, reported as odds ratio with 95% confidence interval	6 and 12 mo
	Quantitative isotope uptake in CNO-lesions by SUV_max_			GLMM with ANCOVA	6 and 12 mo
**Correlations**	SUV_max_ with maximal and average pain	[^18^F]NaF-PET/CT and BPI	0, 6, and 12 mo	Pearson’s R or Spearman’s Rho as appropriate	0, 6, and 12 mo
	SUV_max_ with ESR and CRP	[^18^F]NaF-PET/CT and standard laboratory evaluation	0, 6, and 12 mo		
**Predictors of treatment response**	Diagnostic delay (yr)	-	0 mo	GLMM in pamidronate group, with maximal pain score on BPI as outcome	6 mo
	Baseline lesional isotope uptake (SUV_max_)	[^18^F]NaF-PET/CT	0 mo		
	Degree of central sensitization	CSI	0, 6, and 12 mo		
	Degree of neuropathic pain	PAIN-DETECT	0, 6, and 12 mo		
	Baseline presence of erosions, hyperostosis, and/or ankylosis	[^18^F]NaF-PET/CT	0 mo		
	Baseline presence of elevated ESR and/or CRP	-	0 mo		
**Cost-effectiveness**	Trial-based cost-utility from a societal perspective in accordance with the Dutch health-economics guidelines	IPCQ	0, 3, 6, 9, and 12 mo	Trial-based cost-utility analysis with costs-per-quality adjusted life yr, based on net-benefit analysis and friction-cost method.	6 and 12 mo (extrapolated to life-long discounted time horizon)

Abbreviations: ANCOVA; Analysis of Covariance, [18F]NaF-PET/CT; Sodium-fluoride positron emission tomography, BPI; Brief Pain Inventory, CarerQoL; Care-related Quality of Life Instrument, CNO; Chronic Nonbacterial Osteitis, COXIBs; Cyclooxygenase 2 Inhibitors, CSI; Central Sensitization Inventory, FACS; Fluorescence Activated Cell Sorting, ELISA; enzyme-linked immunosorbent assay, EQ-5D; EuroQol 5-Dimension, ESR; Erythrocyte Sedimentation Rate; GLMM; Generalized Linear Mixed Model, IPAQ; International Physical Activity Questionnaire, MLPA; Multiplex Ligation-dependent Probe Amplification, MVI-20; Multidimensional Fatigue Inventory-20, NRS; Numerical Rating Scale, NSAIDs; Non-Steroidal Anti-Inflammatory Drugs, PGIC; Patient Global Impression of Change, SF-36; Short Form Health Survey, SRQ; Shoulder Rating Questionnaire, SUV_max_; Standardized Maximum Uptake Value.

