A third challenge encountered in this trial was the choice for the primary outcome of patient-reported pain. Ideally, we would use a composite score that includes patient-reported outcomes such as pain and objective measures of inflammatory activity, reflecting both patient relevance and the biological mechanisms of treatment. However, for CNO, no objective markers of inflammatory activity are currently proven. Systemic inflammation markers are suboptimal indicators of disease activity due to their frequently normal levels at diagnosis,^2^ and the same holds for radiologic signs of disease activity such as increased isotope uptake, since it has been shown to persist despite evident clinical improvement, which may prompt overtreatment.^49^ Consequently, we use patient-reported pain at the site of CNO bone lesions as the primary outcome of this trial. While this is most relevant for patients, it may be modulated via different mechanisms which may complicate interpretation of the results. Therefore, patients are clearly instructed to differentiate and score the nociceptive inflammatory bone pain.^53^ Additionally, neuropathic and nociplastic pain are measured with standardized questionnaires to explore their association with treatment response. Recognizing that radiologic signs of disease activity in CNO need to be further investigated, this trial includes quantified uptake on [^18^F]NaF-PET/CT in the secondary analyses. This imaging modality is sensitive for bone pathology and yields quantitative parameters of bone turnover, which have shown to be elevated in CNO lesions and correlate with ESR.^46^ The longitudinal data on quantified [^18^F]NaF uptake from this trial will further elucidate the working mechanism of pamidronate, revealing whether pamidronate can quantitatively reduce bone turnover, and whether a decrease is associated with a reduction in pain.

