A final essential consideration of the PAM-CNO trial will be whether its results will be applicable to the pediatric CNO population as well. From a clinical perspective, there are similar observational data supporting the use of pamidronate in pediatric CNO, and this trial may reinforce the clinical body of evidence.^25^^,^^54^ From a pathophysiological perspective, it appears that adult and pediatric CNO may share common auto-inflammatory mechanisms, which may lend further credence to the use of pamidronate in both age groups.^55^ Therefore, results of the PAM-CNO trial may extrapolate to pediatric CNO, especially since bisphosphonates have shown to be safe and well-tolerated in children too.^56^

In conclusion, this first RCT on the effectiveness of pamidronate in adult patients with CNO is expected to have a significant impact, as there is currently no established treatment for this rare condition. Should pamidronate be found effective for pain control, future research should explore the optimal dosage and treatment schedule, and identify specific patient subgroups which may benefit the most. Also, pamidronate should be compared against TNFi which is commonly also used as second-line treatment in adult CNO. Additionally, this study will provide useful information on whether quantified [^18^F]NaF uptake can serve as an indicator of disease activity and treatment response in adult CNO. If the data support this idea, subsequent studies may consider this parameter when developing composite scores for disease activity in adult CNO.

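### SUVmax and pain are correlated only as levels at each visit, which cannot show whether a fall in uptake goes with a fall in pain

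*Protocol article*

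**What the plan says.** The section Outcomes and statistical analyses lists among the secondary outcomes the "biochemical, and radiological outcomes, as well as their intercorrelation", and sends the reader to Table 1 for instruments, methods and timepoints. The Correlations block of Table 1 gives the pair as "SUV_max_ with maximal and average pain", the method as "Pearson’s R or Spearman’s Rho as appropriate", and the analysis timepoints as 0, 6 and 12 months.

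The aims are wider. The additional objectives include "to elucidate mechanisms by which pamidronate may reduce pain in CNO, and cost-effectiveness". The Discussion expects the repeated scans to clarify how the drug works, and describes them as "revealing whether pamidronate can quantitatively reduce bone turnover, and whether a decrease is associated with a reduction in pain". Its conclusion adds that the study will inform "whether quantified [^18^F]NaF uptake can serve as an indicator of disease activity and treatment response in adult CNO".

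Entry to the trial requires "Score for maximal pain (concerning bone pain at lesion sites over the past week) ≥6/10".

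**The concern.** Whether a decrease in uptake accompanies a decrease in pain is a question about change within patients. A correlation of levels at one visit is driven largely by lasting differences between patients, such as lesion size, bone density and the way a person uses a pain scale. It can be high when the two measures do not move together, and low when they do.

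Two conclusions depend on this: how pamidronate works, and whether SUVmax can track response to treatment. The Discussion says a favourable answer could bring SUVmax into later composite activity scores. It also notes that raised uptake has been seen to persist in patients who clearly improve clinically. That is a dissociation of changes, and level correlations cannot test it.

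A smaller point concerns month 0. Only maximal pain scores from 6 to 10 can enter, so the month-0 correlation with maximal pain is attenuated. Average pain has no entry threshold.

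**Working it through.** **1. Which analyses use SUVmax?** All are in Table 1 of the protocol article.

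- SUVmax as an outcome, GLMM with ANCOVA at 6 and 12 months: shows whether uptake differs by arm, not whether its fall tracks pain.
- SUVmax with maximal and average pain, at 0, 6 and 12 months: levels, because month 0 has no change and no change variable is named.
- SUVmax with ESR and CRP: does not involve pain.
- Baseline SUVmax as a predictor of 6-month pain, pamidronate arm only: does not use change in SUVmax.

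None relates change in uptake to change in pain. The article gives no expected SUVmax–pain correlation, so there is no figure of its own to reproduce.

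**2. Do level correlations fix the change correlation?** Take unit variances and the following quantities:

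- `L`: SUVmax–pain correlation within a visit, the same at 0 and 6 months
- `c`: SUVmax–pain correlation across visits
- `aS`: correlation of SUVmax between 0 and 6 months
- `aP`: the same for pain, 0.479 (protocol article, Sample size)

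Then

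`r(change) = (2L − 2c) / √[(2 − 2aS)(2 − 2aP)]`

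With L = 0.40 and aS = 0.7 (both assumed), the denominator is √(0.6 × 1.042) = 0.791.

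| c | r(change) |
|---|---|
| 0.1 | 0.60/0.791 = 0.76 |
| 0.2 | 0.40/0.791 = 0.51 |
| 0.3 | 0.20/0.791 = 0.25 |
| 0.4 | 0.00 |
| 0.5 | −0.20/0.791 = −0.25 |

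All five rows are admissible covariance matrices. With aS = 0.5 the range is 0.78 to −0.20 (c from 0 to 0.5). With aS = 0.9 it is 0.88 to −0.44 (c from 0.2 to 0.5). The same pair of level correlations therefore fits opposite answers.

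**3. How often would this mislead with 70 patients?** Write each measure as a stable patient part plus an independent visit part. The stable share is 0.479 for pain (from the plan) and 0.7 to 0.8 for SUVmax (assumed). Then

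`level r = r(stable) × √(aS × aP) + r(visit) × √[(1 − aS)(1 − aP)]`, and `r(change) = r(visit)`.

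- (a) Stable parts correlated 0.6, changes unrelated. Level r = 0.6 × √(0.7 × 0.479) = 0.35, or 0.6 × √(0.8 × 0.479) = 0.37. The true change correlation is 0.
- (b) Visit parts correlated 0.5, stable parts unrelated. Level r = 0.5 × √(0.3 × 0.521) = 0.20, or 0.5 × √(0.2 × 0.521) = 0.16. The true change correlation is 0.5.

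Simulating 20,000 trials of 70 patients (critical |r| = 0.235) gives, at month 6:

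| Case | Mean level r | Level r significant | Change correlation significant |
|---|---|---|---|
| (a) | 0.34–0.37 | about 84–90% | 5% (nominal) |
| (b) | 0.16–0.20 | 27–38% | over 99% |

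**4. Range restriction at month 0.** I simulated an integer 0–10 pain score with unselected mean 6–7 and SD 2–2.5 (assumed), and kept scores of 6 or more. A true correlation of 0.40 falls to 0.26–0.30.

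**5. Is a change analysis feasible?** By Fisher z, the smallest correlation detectable with 80% power (two-sided 0.05) is tanh[(1.96 + 0.84)/√(n − 3)]. This is 0.33 for n = 70 and 0.46 for n = 35. At n = 70 an observed 0.4 has a 95% CI of 0.18 to 0.58.

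**The case against.** **The full protocol or analysis plan may contain the analysis.** The article is condensed, and a change analysis may exist elsewhere. But the article does not leave this row open. It states the variables, the method and the timepoints, and that analysis does not answer the question it poses in the Discussion.

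**The table never says levels.** This is true. The abstract also describes the pain and bone-turnover outcomes as changes, so the 6- and 12-month entries might be meant as changes. But one row covers all three visits with the same variables, and at month 0 it can only be levels. If changes are intended later, the table should say so.

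**The Discussion does not tie its promise to this row, and levels suit part of the aim.** This stands in part. The between-arm model of SUVmax covers whether turnover falls, and same-visit levels are a sensible look at SUVmax as a marker of disease activity. Neither covers treatment response or the link between the two falls.

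**The two scenarios are extremes.** This is also fair. If stable and visit parts both correlate 0.4 and aS = 0.75, the level r is 0.4 × [√(0.479 × 0.75) + √(0.521 × 0.25)] = 0.38, against a change correlation of 0.40. The two can agree, but the planned analysis cannot tell whether they do.

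**Range restriction is overstated, because the plan gives an SD of 2 for patients scoring 6 or more.** Against an unselected SD of 2–2.5, an SD of 2 would leave the correlation at about 0.33–0.40. However, scores confined to 6–10 with mean 8 have SD at most √[(10 − 8)(8 − 6)] = 2, reached only if every patient scores 6 or 10. The attenuation is a side point, and the main concern does not need it.

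**Conclusion.** The concern holds. Following Table 1 as written would not show whether a fall in uptake goes with a fall in pain, and the resulting conclusion on mechanism or treatment response could be wrong in either direction. The size depends on assumptions: only the 0.479 and the 70 patients come from the plan, while the stable share of SUVmax variance and the stable and visit correlations are assumed. The mismatch itself does not depend on them, since level correlations of 0.40 at both visits are compatible with change correlations from 0.76 to −0.25 at aS = 0.7. This is a secondary, mechanistic analysis. The primary endpoint and the treatment-effect estimates are untouched, so the correction is advisable rather than critical.

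**What to change.** Add to Table 1, as the mechanism analysis, a regression of the 0-to-6-month change in maximal pain (and likewise average pain) on the 0-to-6-month change in SUVmax. Use one value per patient, adjust for both baseline values and arm, and report the partial correlation with its 95% CI. Adjusting for arm keeps a shared treatment effect from posing as a patient-level link. Adjusting for baseline pain deals with regression to the mean after selection at 6 or more.

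Report the plain change correlation beside it. In case (a) above, the partial correlation given both baselines is still about 0.09–0.10 rather than 0, because a single baseline does not fully remove a stable trait. In case (b) it is about 0.44. Both are computed from the covariance matrices implied by that model.

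Keep the level correlations at 0, 6 and 12 months as descriptive, and note that the month-0 one with maximal pain is range-restricted by the entry criterion. If the change analysis is not wanted, the Discussion's statement should be reworded instead.

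The cost is one regression per pain score and some wording. SUVmax and BPI pain are already collected at 0, 6 and 12 months. It is best settled before unblinding, so that the mechanism result is not post hoc.

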### Sample size

Based on our observational data on adult CNO patients with a maximum pain score of ≥6/10 treated with intravenous pamidronate, BPI score for maximal pain is expected to decrease from a mean of 8 with standard deviation (±) of 2 to a mean of 6 ± 2 in the active treatment arm. In rheumatoid arthritis, the placebo effect on pain has been estimated at 16-22 at a 100-mm scale.^44^ However, because evidence-based treatments for CNO are entirely lacking—potentially reducing patient confidence in any given treatment—and many patients present with advanced disease due to diagnostic delays, we anticipate a smaller effect in the placebo arm of this trial, with pain levels decreasing from 8 ± 2 to 7.5 ± 2. We use a power of 80% and an alpha of 0.05. As the primary analysis is done with ANCOVA, adjustment for correlation between baseline and follow-up scores was done (Pearson’s correlation coefficient calculated at 0.479), with a required sample size of 35 patients per arm (total *n* = 70).^45^ In case of screen failure or drop-out before the 6-mo primary endpoint, patients will be replaced to meet the required sample of 70.

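### The predictor analysis in Table 1 names no adjustment for baseline pain, so as written it models the 6-month pain level and flags too often factors that merely track baseline pain

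*Protocol article*

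**What the plan says.** The Objectives section of the protocol article states the aim: "Additional objectives are to evaluate baseline predictors of treatment response". In Table 1 (Outcomes and statistical analyses), the block on predictors of treatment response lists six factors: diagnostic delay, baseline lesional SUVmax, central sensitization, neuropathic pain, structural lesions at baseline, and raised ESR or CRP. The analysis for all six is a "GLMM in pamidronate group, with maximal pain score on BPI as outcome", at 6 months. Baseline pain is not on the list.

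For the primary outcome, the text above the table uses a "generalized linear mixed model (GLMM) with analysis of covariance (ANCOVA) to account for baseline scores". Table 1 repeats the label GLMM with ANCOVA for the primary outcome, the other BPI pain scores, the biochemical markers and SUVmax. The predictor row and the pain diary row say GLMM only.

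The Sample size section supplies the two figures used below: "Pearson’s correlation coefficient calculated at 0.479" and "with a required sample size of 35 patients per arm".

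**The concern.** Elsewhere the article treats response as relative to the starting point. The Abstract gives the primary outcome as a change from 0 to 6 months, and Table 1 includes a reduction of at least half in maximal pain. A predictor of response should therefore be associated with 6-month pain beyond what baseline pain already explains.

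The row as written fixes the arm, the model family, the outcome (the score itself, not its change) and the timepoint, and names no baseline term. That model tests association with the 6-month level. Because baseline and follow-up pain are correlated, any factor that goes with higher baseline pain is also associated with higher 6-month pain, even if it says nothing about improvement. The central sensitization and neuropathic pain scores are plausible examples, and the Discussion says these pain types are measured to explore their association with treatment response. At stake is the labelling of markers of high starting pain as predictors of poor response, and some power in an analysis of about 35 patients.

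**Working it through.** **Inputs.** The correlation of baseline with follow-up pain is 0.479, and n = 35 is the planned pamidronate arm (both from Sample size). The test is at 5%, taken as two-sided because the article does not state sidedness. The correlation r between a candidate factor and baseline pain is not given anywhere, so it is an assumption, shown as a range.

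**The plan's own figure.** The article gives no operating characteristics for this analysis. The 35 per arm is used only as the number of patients in the model. It is not reproduced from the stated inputs ("to a mean of 6 ± 2 in the active treatment arm" against placebo "with pain levels decreasing from 8 ± 2 to 7.5 ± 2", so a difference of 1.5 with SD 2, and "We use a power of 80% and an alpha of 0.05"):
- with ANCOVA: 2 × (1.960 + 0.842)² × 2² × (1 − 0.479²) / 1.5² = 21.5, so 22 per arm;
- unadjusted: 27.9, so 28 per arm.

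Nothing in this point depends on how 35 was reached.

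**Step 1: the induced correlation.** If a factor is related to 6-month pain only through baseline pain, its correlation with 6-month pain is 0.479 × r. This is 0.096, 0.144, 0.192 and 0.240 for r = 0.2, 0.3, 0.4 and 0.5. Given baseline pain, its association with 6-month pain is zero.

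**Step 2: rejection rates.** Normal data, n = 35, 20,000 simulated trials per setting, two-sided 5% test of the factor:

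| r | without baseline pain | with baseline pain |
|---|---|---|
| 0 | 4.8% | 4.9% |
| 0.2 | 8.3% | 4.9% |
| 0.3 | 13.1% | 5.0% |
| 0.4 | 19.1% | 4.6% |
| 0.5 | 28.8% | 5.1% |

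A hand check at r = 0.5 with Fisher's z: atanh(0.2395) × √(35 − 3) = 0.244 × 5.657 = 1.38. The chance that a standard normal exceeds 1.96 − 1.38 = 0.58 is about 28%, in line with the table.

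**Step 3: precision.** Baseline pain removes 0.479² = 23% of the variance of 6-month pain. For a real predictor unrelated to baseline pain, with a standardised effect of 0.4, simulated power at n = 35 rises from 68% without baseline pain to 80% with it.

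**Step 4: a different null.** Suppose instead that the expected change is the same at every value of the factor, so that the factor has correlation r with both baseline and 6-month pain. Its partial correlation given baseline is then (r − 0.479r) / √((1 − r²)(1 − 0.479²)), which is 0.12 at r = 0.2 and 0.34 at r = 0.5. The adjusted model rejects in about 10% of trials at r = 0.2, rising to 52% at r = 0.5. The unadjusted model rejects in 21% rising to 89%. Adjustment is clearly better here too, but does not restore 5%.

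**The case against.** **The omission is inferred.** No sentence says that baseline pain is left out. The evidence is a short cell in a condensed article, the full protocol exists elsewhere, and the pain diary row also lacks the ANCOVA label. This stands as a limit on certainty: a reader might infer that the investigators have decided against adjustment, and the article does not show that. The cell is nonetheless a stated model that departs from its neighbours in the table, not mere silence.

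**The simulation is ordinary regression, not a mixed model.** A mixed model could carry the 0-month score as a repeated outcome with a factor-by-time term, which would test change. That is fair, but no such term is stated. With only a factor main effect, baseline pain would be averaged in and the model would still not test response.

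**The size rests on assumed correlations.** This is correct. Patients are told to score inflammatory bone pain separately, and entry at 6/10 or more restricts the baseline range; both could weaken the link. If full-range pain were normal with mean 6 and SD 2, restricting it to 6 to 10 would shrink a correlation of 0.5 to 0.28. The lower end of the range is at least as plausible as the upper.

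**The restored 5% depends on the null chosen.** This stands, as Step 4 shows.

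**The analysis is exploratory.** A reader might infer that the trial will use it to select subgroups for treatment. The Discussion leaves identifying such subgroups to future research; the trial's own aim is only to evaluate baseline predictors.

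**Conclusion.** The point holds for the row as written: without baseline pain the model targets the 6-month pain level, and factors that only track baseline pain are flagged too often. The size is about 8% to 29% instead of 5% at n = 35. It rests on assumed factor-baseline correlations of 0.2 to 0.5, the article's 0.479, a single 6-month regression, and a factor acting on 6-month pain only through baseline pain.

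Two stronger readings are not supported. One is that such factors will come out as predictors: even at r = 0.5, about 71% of such tests would be non-significant, so this is an inflated error rate, not a certain false finding. The other is that adding baseline pain turns the analysis into a test of who responds to pamidronate. Within one arm, a factor that predicts the course of pain under any treatment cannot be told apart from one that modifies the drug's effect; separating them needs the placebo arm and a factor-by-treatment term. The analysis is secondary, and the primary comparison is unaffected.

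**What to change.** In Table 1, change the predictor row to GLMM with ANCOVA and state that the 0-month maximal BPI pain score is a covariate in every predictor model. If the full protocol or analysis plan already includes it, the row need only say so. Replacing the outcome by the change score without baseline as a covariate is no substitute: in the Step 2 simulation it rejects in 8.6% to 32.5% of trials for r = 0.2 to 0.5.

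Describe each coefficient as an association with 6-month pain given baseline pain within the pamidronate arm, that is, as prognostic and not as proof of differential treatment response.

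The cost is one degree of freedom and a change of wording before unblinding; the covariate is already collected.
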